|                                          | 
Secondary criteria
 
Axis 1:
 
1) a) b) Actigraphy (rhythm amplitude and acrophase); Sleep diary (scores), Diurnal cortisol (cortisol levels); Polysomnography (sleep efficiency and wakefulness numbers); ISI, PSQI questionnaires (scores)
 
2) Neuropsychological tests (scores); Spatial memory task (scores); fMRI activation - ANT task (task-related BOLD signal - effective connectivity)
 
3) aMRI (cortical structures - white and gray matter)
 
4) fMRI at rest (dynamic fluctuations of the BOLD signal - functional connectivity, corrected for cardiorespiratory confounding factors); Post-MRI debriefing questionnaire (scores)
 
5) a) Polysomnography (sleep efficiency and number of awakenings); ISI, PSQI questionnaires (scores); HVLT (scores); Spatial memory task (scores); aMRI: (cortical structures - white matter); STAI, BDI-II questionnaires (scores)
 
5) b) Polysomnography (sleep efficiency and number of awakenings); ISI, PSQI questionnaires (scores); CAR and pre-post MRI cortisol (cortisol levels)
 
5) c) Polysomnography (sleep efficiency and number of awakenings); ISI, PSQI questionnaires (scores); Quality of life questionnaires (scores)
 
Axis 2:
 
1) a) Actigraphy (rhythm amplitude and acrophase); Sleep diary (scores); Diurnal cortisol (cortisol levels)
 
1) b) Spatial memory task (scores)
 
1) c) CAR and pre-post MRI cortisol (cortisol levels)
 
2) Actigraphy (rhythm amplitude and acrophase), Sleep diary: (scores); Polysomnography (sleep efficiency and number of awakenings); ISI, PSQI questionnaires (scores)
 
3) Polysomnography (sleep efficiency and number of awakenings); ISI, PSQI questionnaires (scores); Neuropsychological tests (scores); Quality of life questionnaires (scores)
 |

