## 8 STUDY PLAN

### 8.1 METHODOLOGY

The ICANSLEEP project is a bicentric longitudinal study.

Data from 25 patients with localized breast cancer treated with chemotherapy will be compared with those from a group of 25 patients not treated with chemotherapy and a group of 25 cancer-free volunteers (control groups), matched for sex, age and years of education (Barbizet scale).

The various evaluations will be carried out as follows:

- At T1: Approximately 1.5 months after surgery and before the start of chemotherapy in the CHI group and before the start of radiotherapy in the NCH group,
- At T2: after a delay of around 6 months, within 2 weeks of the end of chemotherapy for the CHI group, or at a distance from radiotherapy for the NCH group,
- At T3: after a two-week intervention with GVS versus non-effective stimulation (known as SHAM). To assess the effect of GVS, patients will be assigned to either the effective GVS group or the SHAM group (random selection). SHAM stimulation involves using the device but receiving a very low-frequency current that has no effect on the vestibular system. This approach has already been used and validated in the COMETE unit (Caen, [name]) with which we collaborate. All cancer-free volunteer participants will undergo GVS.

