### 9.1.1 Self-assessment of sleep and circadian typology

Sleep questionnaires (ISI and PSQI) are to be completed at home between the two evaluation sessions, to provide information on subjective sleep parameters. The ISI focuses specifically on insomnia-related symptoms, while the PSQI measures participants' overall subjective sleep quality. The Horne and Ostberg questionnaire  provides information on circadian typology.

THE ISI  is a 7-item Likert scale assessing symptoms associated with insomnia. A score above 8 indicates the presence of a complaint associated with insomnia.

The PSQI  is a questionnaire evaluating 7 components associated with sleep (quality, duration, sleep onset latency, sleep efficiency, use of hypnotics, sleep alterations and impact on daytime functioning). The score ranges from 0 to 21, with a score of 5 or more considered to represent a complaint of poor sleep.

Horne and Ostberg's circadian typology questionnaire  includes 19 items to determine circadian typology (very much morning, moderately morning, neutral, moderately evening, very much evening) on the basis of a total score between 16 and 86.

All 3 questionnaires can be completed in 15 minutes.

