### 9.1.4 Physiological measurements related to circadian rhythms and stress response

Repeated saliva sampling will be carried out at each stage of the study (*Table 3*) to study changes in salivary cortisol levels, one of the markers of circadian rhythms, as well as certain stress-related responses (*Cortisol Awakening Response*).

**Table 3** Cortisol measurements according to evaluation times

|                                                     | T1 and T2 | T3 |
|-----------------------------------------------------|-----------|----|
| Before and after MRI                         | •         |    |
| CAR
- Waking up
- 30 min.
- 45 min. | •         | •  |
| Bedtime                                      | •         | •  |
| Before and after rest                        | •         | •  |
| Total measurements                           | 8         | 6  |

**Note.** CAR: Cortisol Awakening Response

Participants will be provided with Salivette® systems for saliva testing. This device involves inserting a cotton ball into the mouth and soaking it in saliva for 2-3 minutes, then returning it to the storage tube.

Participants will receive a description of the procedure to remind them of the instructions (no drinking, no eating, no smoking, no brushing teeth in the 30 minutes prior to collection) and a table to enter the time of collection. Morning samples will be collected at the participant's home or hotel, and placed in an insulated bag to be stored at 4°C before being transported to the laboratory in the morning. The remaining samples will be collected in our research unit. All salivary samples will be centralized and stored at -80°C at the Centre François Baclesse, in a secure environment with optimum traceability. These samples will be sent to [name]'s team in Rouen (Inserm, U1239, Dir: [name]) for salivary cortisol determination. Parameters that may influence salivary cortisol levels will also be collected (age, body mass index, smoking habits, contraceptive methods, socio-educational status).

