### 12.2 STATISTICAL ANALYSIS

**Axis 1:** In order to characterize the sleep of breast cancer patients before and after adjuvant chemotherapy, sleep parameters measured by polysomnography (in particular sleep efficiency and number of awakenings) or by questionnaire will be described in terms of headcount for qualitative variables, and mean and standard deviation (or median and range) for quantitative variables, at T1 and T2 in each of the groups of interest. Similarly, circadian rhythm parameters measured by actigraphy (e.g. mean amplitude over a week) or by salivary cortisol assay will be described at each time and by group. To assess the effect of cancer on sleep and circadian rhythm, parameters at T1 and T2 will be compared between patients and controls using a Chi test or a Student (or Wilcoxon) test. To assess the effect of chemotherapy on sleep and circadian rhythm, the parameters of chemotherapy-treated patients will be compared between T1 and T2 by a McNemar test or a Student (or Wilcoxon) test for paired series. Alternatively, the effect of chemotherapy on T2 parameters can be tested in linear or logistic models adjusted for T1 parameters. Relationships between sleep parameters and circadian rhythm parameters will be assessed using a correlation matrix (Pearson's or Spearman's). The relationship between sleep parameters and scores on cognitive tests and quality-of-life assessments can be assessed at any time using a linear mixed model (taking into account correlation between repeated measures of the same subject).

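### The effect of cancer on cortisol and acrophase is tested without adjustment, although unmatched influences on these outcomes (BMI, smoking, contraception, chronotype) are collected

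*Protocol*

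**What the plan says.** **Outcomes.** The synopsis and Table 2 (section 7.2) list, for Axis 1 objectives 1 a and b, "Actigraphy (rhythm amplitude and acrophase); Sleep diary (scores), Diurnal cortisol (cortisol levels"), together with polysomnography and sleep questionnaires.

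**Analysis.** For the effect of cancer, section 12.2 states that "parameters at T1 and T2 will be compared between patients and controls" by a Chi-squared "test or a Student (or Wilcoxon) test. To assess the effect of chemotherapy on sleep and circadian rhythm" the same section turns to paired tests within the chemotherapy group. It then offers "linear or logistic models adjusted for T1 parameters" as an alternative, for the chemotherapy effect only. No adjusted option is given for the effect of cancer. The Axis 2 mixed model is adjusted for group and possibly chemotherapy, not for chronotype or the cortisol factors.

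**Collected variables.** Section 9.1.4: "Parameters that may influence salivary cortisol levels will also be collected (age, body mass index, smoking habits, contraceptive methods, socio-educational status"). Section 9.1.1 says that the Horne and Ostberg questionnaire "provides information on circadian typology"; sections 8.4.4 and 8.4.5 schedule it at T1, T2 and T3. It appears in no criterion in Table 2 and in no analysis in section 12.2.

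**Design control.** Section 8.1 describes the groups as "matched for sex, age and years of education (Barbizet scale"). Sections 8.3, 8.3.3 and 8.4.1.2 repeat the matching on age and education and add no other factor.

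**The concern.** The comparison of patients with controls is observational. Matching deals with sex, age and education. It leaves open chronotype, which concerns the timing of daily activity, and three factors that the protocol itself names as possible influences on cortisol. A two-sample test attributes the whole group difference to group membership, so a systematic difference in smoking or body mass index, for example, would appear in the report as an effect of cancer on cortisol.

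The recruitment routes make such differences plausible without proving them. Patients come from one cancer centre (section 8.3), while controls come through acquaintances, associations and similar groups (section 8.4.1.2). Controls must not work shifts (section 8.3.3); the patient criteria in sections 8.3.1 and 8.3.2 contain no such rule.

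Even if the groups are alike on these traits, leaving them out keeps explainable variation in the error term of a comparison with only 25 controls.

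**Working it through.** The protocol gives no power, significance level, effect size or standard deviation (section 12.1), so there is no stated figure to reproduce. What follows is an illustration.

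**Inputs from the protocol**
- 50 patients (25 + 25) and 25 controls (section 12.1), taking patients as one pooled group.

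**Assumed inputs, not in the protocol**
- Outcome SD set to 1; two-sided 5% test.
- Correlation *r* between covariate and outcome: 0.3 to 0.6. For several covariates together, read *r* as the multiple correlation in the precision step.
- Systematic patient-control gap in the covariate: 0.2 to 0.5 SD.

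**1. Role of each collected variable**

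| Variable | Matched | Used in 12.2 |
|---|---|---|
| Age | yes | no |
| Education (covers at least part of socio-educational status) | yes | no |
| Body mass index | no | no |
| Smoking | no | no |
| Contraception | no | no |
| Horne and Ostberg score | no | no |

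**2. Bias if there is a systematic gap** (bias = *r* × gap)
- Low end: 0.3 × 0.2 = 0.06 SD.
- High end: 0.6 × 0.5 = 0.30 SD.

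The standard error of the unadjusted difference is sqrt(1/50 + 1/25) = 0.245 SD. With no true effect of cancer, the noncentrality is 0.06/0.245 = 0.24 to 0.30/0.245 = 1.22. On 73 degrees of freedom, the nominal 5% test then rejects in about 6% to 23% of studies.

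**3. Precision if there is no systematic gap** (adjusted SE / unadjusted SE = sqrt(1 − *r*²))
- *r* = 0.3: sqrt(0.91) = 0.954, a reduction of about 5%.
- *r* = 0.6: sqrt(0.64) = 0.80, a reduction of 20%. Put the other way, the unadjusted error is 1/0.80 = 1.25 times the adjusted one.

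| | Unadjusted | *r* = 0.3 | *r* = 0.45 | *r* = 0.6 |
|---|---|---|---|---|
| Difference detectable with 80% power (SD) | 0.69 | 0.66 | 0.61 | 0.55 |
| Power for a 0.5 SD difference | 53% | 57% | 63% | 72% |

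These figures ignore the small loss from covariate imbalance and the few degrees of freedom used.

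**The case against.** **This could be left to the SAP.** Covariate lists for secondary, exploratory comparisons often are, the study calls itself descriptive and exploratory, and the stated reason for collecting the cortisol factors is compatible with later adjustment. This lowers the stakes: in Axis 1, acrophase and cortisol are secondary, behind polysomnographic sleep efficiency and awakenings. It does not remove the point, because section 12.2 does more than stay silent. It names an unadjusted test for this comparison, while it names covariates for others.

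**Chance imbalance is not bias.** A reader might infer that likely chance differences in chronotype between 50 patients and 25 controls measure the error credited to cancer. They do not. Variation of that kind is already in the outcome SD and so in the standard error of the t test, which keeps its nominal error rate. Bias needs a systematic gap, and the protocol gives no evidence of its size.

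**Not every listed factor is ignored.** A reader might also infer that all five influences listed in section 9.1.4 have no role. Age is matched, and education covers at least part of socio-educational status.

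**Adjusting acrophase for chronotype may remove the effect sought.** This objection stands. The T1 score is a self-report taken after diagnosis and surgery, and section 6 expects rhythms to be altered in patients already before chemotherapy. Chronotype at T1 may therefore be partly a consequence of cancer, and an adjusted model should not replace the planned acrophase comparison. Body mass index, smoking and contraception at T1 are also recorded after diagnosis, which is why the unadjusted cortisol result should stay in view.

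**Conclusion.** The point holds in a limited form. Section 12.2 fixes unadjusted tests for a non-randomised comparison, while body mass index, smoking, contraception and chronotype are collected but neither matched nor analysed.

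The harm is conditional. A systematic gap of 0.2 to 0.5 SD with a correlation of 0.3 to 0.6 would bias the contrast by 0.06 to 0.30 SD. Without such a gap the loss is precision only, with a standard error that adjustment could lower by about 5% to 20%. Both ranges rest wholly on assumed correlations and gaps. The documents do not support a claim that the groups do differ on these traits, or that the planned tests are invalid.

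The case for adjusting the cortisol comparison is clear, since the protocol names the influences itself. For chronotype and acrophase it supports a sensitivity analysis and no more.

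**What to change.** In section 12.2, Axis 1:

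- **Cortisol.** Compare each cortisol measure between patients and controls at T1 and T2 with a linear model containing group, the matching variables (age, education) and body mass index, smoking and contraception as recorded at T1. Transform the measure if it is skewed. Report the unadjusted comparison alongside.
- **Acrophase.** Keep the planned comparison. Add a pre-specified sensitivity analysis adjusted for the T1 Horne and Ostberg score, with a note that the score is measured after diagnosis and may itself be affected by cancer.
- **Section 9.1.4.** State that the cortisol factors are recorded at T1; the section does not now name the visit.

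The cost is wording and a few degrees of freedom. If each covariate takes one, the residual degrees of freedom fall from 75 − 2 = 73 to 75 − 7 = 68 for cortisol. The variables are already planned, so no participants or visits are added. With 75 participants the covariate list should stay short and be fixed in advance.

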| Number of patients required                   | 
 
• 25 patients treated with chemotherapy for operated localized breast cancer
 
• 25 patients not treated with chemotherapy for operated localized breast cancer
 
• 25 breast cancer-free female volunteers of the same age
 
 
A total of 75 participants, including 50 patients and 25 breast cancer-free women
                                                                                                                                                                                                                                                                                                                                                                                                                                                                                                                                                                                                                                                                                                                                                                                                     |
| Participating centers                         | 
Center François Baclesse (patient recruitment), Caen, France
 
Unit 1077 (recruitment of healthy subjects), Caen, France
                                                                                                                                                                                                                                                                                                                                                                                                                                                                                                                                                                                                                                                                                                                                                                                                                                                                                                                                                                                                                                                     |
| Study duration                                | 48 months                                                                                                                                                                                                                                                                                                                                                                                                                                                                                                                                                                                                                                                                                                                                                                                                                                                                                                                                                                                                                                                                                                                                                                                |

## 2 LIST OF ABBREVIATIONS

ANT: Attentional Network Test

BDI: Beck Depression Inventory

Brief COPE: Brief Coping Orientation to Problems Experienced

BPI: Brief Pain Inventory

CAR: Cortisol Awakening Response

FACIT-F: Functional Assessment of Chronic Illness Therapy - Fatigue

FACT-Cog: Functional Assessment of Cancer Therapy - Cognitive Function

FACT-G: The Functional Assessment of Cancer Therapy - General

GVS: Galvanic Vestibular Stimulation

HVLT: Hopkins Verbal Learning Test

IPAQ: International Physical Activity Questionnaire

ISI: Insomnia Severity Index

KSS: Karolinska Sleepiness Scale

MDC: Memory for numbers

MFI-20: Multidimensional Fatigue Inventory

MoCA: Montreal Cognitive Assessment

Oth: Comments from Others

PCA: Perceived Cognitive Abilities

PCI: Perceived Cognitive Impairment

PCL-5: Posttraumatic Stress Disorder Checklist for DSM-5 (Diagnostic and Statistical Manual of mental disorders, 5th version)

PSQI: Pittsburgh Sleep Quality Index

PTGI: Post-Traumatic Growth Inventory

QoL: Quality of Life

STAI-Y: State-Trait Anxiety Inventory

TMT: Trail Making Test

vm: Virtual Meter

### 3 STUDY DIAGRAM

Patients treated with adjuvant chemotherapy (*CHI group*) :

[figure not shown]

Patients not treated with adjuvant chemotherapy (*NCH group*) :

[figure not shown]

Cancer-free female volunteers (*CTL group*) :

[figure not shown]

**Figure 1.** Schematic diagram of the study by group

**Note.** GVS: Galvanic Vestibular Stimulation, SHAM, non-effective stimulation

## 4 SUMMARY OF TESTS TO BE PERFORMED

**Table 1** Summary of assessments offered to participants at different stages of the study

| Assessments                                                                                                                                                                                                                                                                                             | Time | Inclusion | T1
Within one month of inclusion and before the start of treatment (chemotherapy or radiotherapy) | T2
6 months after T1 | T3
2 weeks after T2 |
|---------------------------------------------------------------------------------------------------------------------------------------------------------------------------------------------------------------------------------------------------------------------------------------------------------|------|-----------|------------------------------------------------------------------------------------------------------|-------------------------|------------------------|
| Signature of informed consent                                                                                                                                                                                                                                                                           |      | •         |                                                                                                      |                         |                        |
| Sleep complaints and sleep apnea (questionnaires) :
- ISI
- Berlin Questionnaire                                                                                                                                                                                                                  |      | •         |                                                                                                      |                         |                        |
| Quality and physiology of sleep and circadian rhythms
- Questionnaires (home): ISI, PSQI, Horne and Ostberg
- Actigraphy and sleep diary (over the 2 weeks preceding each evaluation period T1, T2 and T3)
- Polysomnography
- Diurnal salivary cortisol
- CAR and cortisol pre-post MRI |      |           | •                                                                                                    | •                       | •                      |
| Functional connectivity and cortical structures
- aMRI
- Resting fMRI
- Activation fMRI with attentional task (ANT)
- Physiology associated with MRI (respiration, plethysmography)
- Post-MRI debriefing questionnaire                                                                  |      |           | •                                                                                                    | •                       |                        |
| Spatial memory task                                                                                                                                                                                                                                                                                     |      |           | •                                                                                                    | •                       | •                      |
| Global cognitive ability: MoCA                                                                                                                                                                                                                                                                          |      |           | •                                                                                                    |                         |                        |
| Cognitive battery
- HVLT
- Space Memory Subtest (MEM-III)
- Baddeley's double task
- N-Back
- d2-R
- TMT A and B
- Spelling fluency                                                                                                                                                |      |           | •                                                                                                    | •                       | •                      |

|                                                                                                                                                                                                                                                                                                                                                                                                                                                                                                                             |  |   |   |   |
|-----------------------------------------------------------------------------------------------------------------------------------------------------------------------------------------------------------------------------------------------------------------------------------------------------------------------------------------------------------------------------------------------------------------------------------------------------------------------------------------------------------------------------|--|---|---|---|
| - Stroop                                                                                                                                                                                                                                                                                                                                                                                                                                                                                                                    |  |   |   |   |
| Quality of life (questionnaires) 
 
- FACT-G (home, patients only)
 
- FACIT-F (home, patients only)
 
- MFI-20 (home)
 
- FACT-Cog (home)
 
- KSS
 
- BPI
 
- IPAQ
 
- BDI-II
 
- STAI-Y - status and features
 
- PCL-5 (patients only)
 
- PSS
 
- Brief COPE - modified dispositional "before cancer diagnostic" (patients only, T1 only) and dispositional
 
- PTGI (patients only)
 
 |  | • | • | • |

**Note.** ISI: Insomnia Severity Index; CAR: Cortisol Awakening Response; ANT: Attentional Network Test; MoCA: Montreal Cognitive Assessment; HVLT: Hopkins Verbal Learning Test; MEM-III: Wechsler Clinical Memory Scale - 3ème edition; TMT : Trail Making Test; PSQI: Pittsburgh Sleep Quality Index; FACT-G: Functional Assessment of Cancer Therapy - General; FACIT-F: Functional Assessment of Chronic Illness Therapy - Fatigue; MFI-20: Multidimensional Fatigue Inventory; FACT-Cog: Functional Assessment of Cancer Therapy - Cognitive Function; KSS: Karolinska Sleepiness Scale; BPI: Brief Pain Inventory; IPAQ: International Physical Activity Questionnaire; BDI-II: Beck Depression Inventory, 2nd edition ; STAI-Y: State-Trait Anxiety Inventory ; PSS: Perceived Stress Scale ; PCL-5: Posttraumatic Stress Disorder Checklist for DSM-5 ; Brief COPE: Brief Coping Orientation to Problems Experienced ; PTGI: Post-Traumatic Growth Index

